
### Data management

All data for the individual participants will be collected by the chief investigator and co-investigator therapists who will administer the interventions. Participants will be allocated a participant number for the trial. All case report form (CRF) data will be entered into a password protected data sheet for analysis and storage.

### Sample size

A sample size of 30 participants has been chosen, based on recommendations regarding pilot and feasibility trials evaluating outcomes [77]. Fifteen patients from the intervention group will be included within the qualitative component carried out at 90 days post-randomisation.

### Data analysis

All data from the case report forms (CRF) will be entered into a purposefully designed Excel database and exported into SPSS version 22.0 for analyses. Descriptive statistics will be used to determine the distributions of the data for the intervention and control groups and to test whether statistical assumptions for parametric tests are achieved. Imputation will be used to correct for missing data. Continuous variables that are normally distributed will be compared between the groups at each follow-up using an independent groups *t* test. Effect sizes will be calculated using Cohen’s *d*. Non-parametric analysis will be conducted for continuous variables that are not normally distributed. Categorical variables will be compared with the chi-square statistic. A *p* value of 0.05 will be considered statistically significant. Where appropriate, analyses will be reported with mean differences and 95% CI. Previous values from the same patient will be used for missing data.

In particular, objectives will be analysed as follows:
The utility of the selection of outcome measures will undergo sensitivity analyses in relation to the ease with which they can be administered and will relate to missing data and the identification of both univariate and multivariate outliers. The effect size for the primary outcome variable will be used to determine the required sample size for a fully powered trial.Recruitment and consent rates will be collected and analysed to determine the feasibility of recruiting form the chosen population. The inclusion and exclusion data (screening log) will be summarised and will influence further protocol changes when considering progression to a full scale randomised controlled trial.Retention rates in response to follow-up procedures (attendance at interviews) will be analysed to identify any trends that may influence further trial progression.The intervention data will undergo sensitivity analyses in relation to non-compliance, the intention to treat per protocol in addition to as treated. Protocol violations regarding the intervention manual strategies will be noted.The intervention effect will be analysed through the use of the above outcome measures, and further analysis of case notes will reveal common trends in treatment adaptation or selection, based on the structure of the intervention manual.

Patient experience, satisfaction with treatment and perceived benefit of participation within the rehabilitation group will be gathered through the semi-structured interviews. The interview data will be transcribed and analysed using thematic analysis [78] to identify key perceptions and self-reported experience and highlight factors that may contribute to future clinical care design. The data will be analysed inductively as little is known regarding the patient experience; therefore, deductive categories cannot be imposed on the data. Two members of the research team will independently code a portion of the data.

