### Data collection

Data on recruitment, including number of eligible and consenting patients and reasons for non-consent, will be collected. Patient demographic data including age, gender, ICU admission diagnosis, co-morbid diseases, date of admission to ICU, ICU length of stay, hospital length of stay, hospital discharge destination and support level required on discharge from hospital will be collected from the medical records. Severity of illness will be measured using the Acute Physiology and Chronic Health Evaluation II (APACHE II) scoring system [59].

Duration of mechanical ventilation will be extracted from the Australia New Zealand Intensive Care Society ANZICS Adult Patient Database (APD). The time schedule for enrollments and administration of assessments and outcome measures is illustrated in Table 4. Retention data including number of withdrawals and reason for withdrawal will be collected. Data will be collected using multiple formal case report forms (CRFs) including pre-screening measures (inclusion/exclusion criteria on all screened patient admissions), admission demographics, pre-intervention checklist for decision making regarding therapy implementation, daily intervention pre- and post-measures, daily control group measures and collation of outcome measures at the three time points. The formal CRFs will be transcribed to an excel spreadsheet for analysis post trial completion. Data forms will be reviewed weekly by the primary investigator to ensure missing data occasions are minimised. Clinical case notes will be audited using a data collection audit checklist.

**Table 4 Tab4:** Time schedule of enrolment and assessments for participants

Measure	Enrolment	Allocation to intervention	ICU Stay	ICU discharge	Hospital discharge	Follow up 90 days
Eligibility screen	x					
Informed consent	x					
Informant Questionnaire on Cognitive Decline in the Elderly (IQCODE)	x					
Demographic		x				
APACHE II		x				
Modified Barthel Index (MBI)	x (Reported)			x	x	x
Grip Strength (Dynamometer)				x	x	x
Functional Independence Measure (FIM)				x	x	x
Short Form (SF-36v2)				x		x
Hospital Anxiety and Depression Scale (HADS)				x	x	x
Confusion Assessment Measure (CAM-ICU)			Daily			
Glasgow Coma Scale (GCS)			Daily			
Short Portable Mental Status Questionnaire (MSQ)			Daily			
Richmond Agitation and Sedation Scale (RASS)			Daily			
Montreal Cognitive Assessment (MoCA)				x	x	x
Dose of Occupational Therapy			Daily			

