#### Secondary outcome measures

The Modified Barthel Index (MBI) [63] is used to measure functional ability and serves as a secondary measure included for its ability to detect change within self-care and functional tasks. The MBI is commonly used in hospital settings, although recent research has highlighted ceiling effects and lack of reliability [64]. The MBI also provides an additional source of comparison across multiple earlier critical care rehabilitation studies. The MBI will be used at multiple time points including allocation to intervention, intensive care unit discharge, hospital discharge and 90-day post-randomisation follow-up.The Montreal Cognitive Assessment (MoCA) [65] is a screening measure of cognition and assesses multiple domains of cognition including attention, memory and visuospatial relations. It is commonly used within the acute and community setting and demonstrates high criterion and convergent validity within the acute care setting [66]. The MoCA will be administered at discharge from intensive care unit, hospital and 90-day post-randomisation follow-up using alternate versions at each time point [67].Grip strength will be measured using a dynamometer (Jamar) [68] at discharge from intensive care unit and hospital and 90-day post-randomisation follow-up. Grip strength is used as a measure of intensive care unit-acquired weakness (ICUAW) and infers a relation between weakness and inability to complete functional activities independently [69].The Short-Form (36) Health Survey (SF-36v2™) will provide a baseline and post discharge measure of participants’ health-related quality of life (HRQOL). The SF-36v2™ is a validated and reliable tool [70] and has been further validated within the critical care setting [71]. This will be completed at intensive care unit discharge and 90-day post-randomisation follow-up.Sedation and delirium status will be measured using the validated Richmond Agitation Sedation Scale (RASS) [46] and the reliable and validated Confusion Assessment Method for ICU (CAM-ICU) [50]. These scores are regularly administered by nursing staff throughout a 24-h period. RASS and CAM-ICU scores immediately prior to and following early occupation-based interventions will be collected for additional analysis. RASS and CAM-ICU scores for the control group participants will be collected daily at 9am.The Glasgow Coma Scale (GCS) [72] is used to evaluate the level of consciousness in patients with neurological conditions or severe injury [73] and will be collected daily at 9 am in the control group, and pre-treatment in the intervention group.Hospital Anxiety and Depression Scale (HADS) [74] is a measure of emotional distress regarding anxiety and depression. It has been validated with the use of critical care survivors [75]. It will be administered at discharge from intensive care unit, hospital and 90-day post-randomisation follow-up.The Informant Questionnaire on Cognitive Decline in the Elderly (IQCODE) (short form) [76] is a reliable and validated measure used to screen for cognitive dysfunction. It will be used as a screening tool for eligibility to the trial and will be completed by the participant’s person responsible.The Short Portable Mental Status Questionnaire (MSQ) [51] is a brief orientation checklist used to demonstrate current and previous memory linked to orientation. It is a 10-statement questionnaire that is easily administered at the bedside. It will be completed pre-and post-treatment in the intervention group, and at 9 am in the control group.

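### Outcomes are compared only by unadjusted tests although pre-admission MBI and APACHE II are collected before treatment; separately, the SF-36 labelled baseline is first taken after the intervention

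*Protocol article*

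**What the plan says.** **The comparison.** The Data analysis section of the protocol article states that normally distributed continuous variables "will be compared between the groups at each follow-up using an independent groups" *t* test. It adds: "Non-parametric analysis will be conducted for continuous variables that are not normally distributed". A *p* "value of 0.05 will be considered statistically significant", Cohen's *d* is reported, and the effect size of the primary outcome is to set the sample size of the full trial. No covariate is named for either type of test.

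**The pre-treatment data.** Under Secondary outcome measures: "The MBI will be used at multiple time points including allocation to intervention". Table 4 puts this first, reported MBI at enrolment. The two places differ slightly, but both precede treatment. Under Data collection: "Severity of illness will be measured using the Acute Physiology and Chronic Health Evaluation II (APACHE II) scoring system". Table 4 places it at allocation. The primary outcome, the FIM, has no pre-randomisation assessment.

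**The SF-36.** Under Secondary outcome measures, the SF-36v2 "will provide a baseline and post discharge measure of" health-related quality of life, and then: "This will be completed at intensive care unit discharge and 90-day post-randomisation follow-up". Table 4 agrees with that timing. The Recruitment section starts treatment between 48 and 72 h after admission, therapy is delivered within the ICU, and the Aims and objectives list ICU discharge as a time at which the effect is evaluated.

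**The concern.** Two separate matters arise.

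First, prior function and severity of illness may predict later function, and the MBI at enrolment is the baseline of the MBI outcome itself. The plan collects both and gives neither a role in the group comparison. With 15 patients per arm, chance differences in these variables will be fairly common. They enter the estimated effect in proportion to their correlation with the outcome, and that effect is meant to size the next trial.

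Second, a value taken after therapy cannot be a baseline. A variable with that name invites a change score or an adjusted model. Either would take away part or all of any benefit already present at ICU discharge.

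**Working it through.** **The plan's own figure.** The total of 30 (15 per arm at 1:1) comes from a recommendation for pilot trials. No difference, SD or power is given, so it cannot be reproduced.

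**Inputs.** n = 15 per arm (Sample size; Design). About 11 per arm at 90 days, from the 75% retention criterion in Table 1 (0.75 × 15 = 11.25). Two-sided 5% level, assumed because 95% CIs are planned. Outcome SD = 1, so results are in SD units. R, the multiple correlation of MBI and APACHE II with the outcome, is not in the documents and is varied from 0 to 0.7.

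**Precision.** The unadjusted 95% half-width is t(0.975, 2n−2) × √(2/n). At n = 15 this is 2.048 × 0.365 = 0.748. With k = 2 covariates it is t(0.975, 2n−2−k) × √[(2/n)(1−R²)(1 + k/(2n−k−3))]. The last factor is the expected cost of chance imbalance in the covariates. At n = 15 and R = 0 this is 2.056 × √(0.1333 × 1.08) = 0.780.

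| R | 15 per arm: half-width (ratio to 0.748) | 11 per arm: half-width (ratio to 0.889) |
|---|---|---|
| 0 | 0.780 (1.043) | 0.947 (1.065) |
| 0.2 | 0.764 (1.022) | 0.928 (1.043) |
| 0.3 | 0.744 (0.995) | 0.903 (1.016) |
| 0.5 | 0.676 (0.903) | 0.820 (0.922) |
| 0.7 | 0.557 (0.745) | 0.676 (0.760) |

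A simulation of 3,000 trials with 15 per arm gave ratios of 1.02, 0.995 and 0.91 at R = 0.2, 0.3 and 0.5. The break-even point is R = √(1 − 1/ratio²), using the ratio at R = 0. It is √(1 − 1/1.043²) ≈ 0.28 at 15 per arm and √(1 − 1/1.065²) ≈ 0.34 at 11 per arm.

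**Chance imbalance.** A covariate differs between arms by more than 0.5 SD with probability P(|Z| > 0.5/√(2/15)) = P(|Z| > 1.37) = 17%. At 11 per arm it is 24%. An imbalance of 0.5 SD moves the outcome difference by 0.5 × r, which is 0.15 SD at r = 0.3 and 0.30 SD at r = 0.6. The standard error of the unadjusted difference is √(2/15) = 0.365 SD.

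**The later trial.** For an assumed d = 0.5 with 80% power, n per arm = 2 × 7.849 × (1−R²)/0.5². This gives 63 unadjusted, and 58, 48 and 33 at R = 0.3, 0.5 and 0.7. An adjusted fit in this trial would give a first estimate of R for that calculation.

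**SF-36.** Let the effect be d1 at ICU discharge and d2 at 90 days, with correlation r between the two scores. The 90-day comparison estimates d2, a change score d2 − d1, and adjustment for the ICU-discharge score d2 − r·d1. Take d2 = 0.5 SD (assumed):

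- d1 = 0.5: change gives 0; adjustment gives 0.35, 0.25 and 0.15 at r = 0.3, 0.5 and 0.7.
- d1 = 0.25: change gives 0.25; adjustment gives 0.425, 0.375 and 0.325.
- d1 = 0: nothing is lost.

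The comparison at each follow-up, which is what Data analysis states, gives 0.5 in every case.

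**The case against.** The case for leaving the tests alone is substantial. Under 1:1 randomisation the *t* test is unbiased, and its standard error already allows for chance imbalance. The Discussion says the trial is not powered to detect clinically significant change. Covariates are often left to an analysis plan, and the article points to a fuller protocol that is not shown. The predictors may be weak: the MBI is a reported value, patients scoring below 40 are excluded, and the article itself acknowledges ceiling effects and poor reliability. Neither covariate is a baseline FIM.

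All of this stands, and it limits the point. A reader might infer that the unadjusted test is wrong or certainly wastes precision. The documents do not support that: they give no correlation, and below about R = 0.3 adjustment gains nothing. A reader might also infer that imbalance passes in full into the FIM difference. It passes only in proportion to the correlation, and a 0.5 SD imbalance at r = 0.3–0.6 moves the estimate by less than one standard error.

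What remains is that the article does fix the form of the comparison, that suitable data are already scheduled, and that the resulting effect size has a stated later use.

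On the SF-36, the objection is that no change score or SF-36-adjusted model appears anywhere. That is correct. The label is still wrong on the article's own timing.

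**Conclusion.** The point holds as a recommendation about the comparison and a correction of a label. It does not show that the planned tests are invalid.

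At 15 per arm, adjusting for enrolment MBI and APACHE II narrows the 95% CI by about 10% if R = 0.5, changes it by 0.5% at R = 0.3, and widens it by 2–4% at R = 0.2 or below. At 11 per arm the corresponding figures are about 8% narrower, 1.6% wider and 4–6% wider. These rest on assumed R and on a linear model with two covariates. Importance is low to moderate for an unpowered feasibility trial; the point matters mainly because the primary effect size will size the full trial.

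The SF-36 at ICU discharge is a post-intervention outcome, and calling it baseline is an error of description. It would be tempting to conclude that the quality-of-life effect will be subtracted away. The stated analysis compares groups at each follow-up and subtracts nothing. The harm would arise only if someone acted on the label.

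**What to change.** 1. In Data analysis, prespecify for each continuous outcome a linear model on arm with enrolment MBI and APACHE II as covariates. Report the adjusted difference with its 95% CI, and the unadjusted difference beside it.
2. In Secondary outcome measures, describe the ICU-discharge SF-36 as the first post-intervention assessment. State that it will not be used to form change scores or as a covariate. Comparing the ICU-discharge and 90-day scores as separate outcomes is what the plan already does.

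Both changes are wording and need no new data. The first costs two degrees of freedom (28 to 26 with 15 per arm, 20 to 18 with 11) and a slightly wider adjusted interval if the covariates predict weakly. The second costs nothing.

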## Methods

### Design

The trial, termed EFFORT-ICU, is a phase II feasibility trial incorporating a mixed methods design. The study follows the guidelines for feasibility trials outlined by the SPIRIT 2013 Statement [39]. EFFORT-ICU is a prospective single-centre, single blinded, equally randomised controlled trial (1:1) comparing standard occupational therapy care to an early enhanced occupation-based therapy. A study overview is shown in Fig. 1. The trial is registered as follows: Australia New Zealand Clinical Trials Registry (ANZCTR): ACTRN12618000374268; prospectively registered on 13 March 2018/https://www.anzctr.org.au.

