### Progression criteria to decide whether to proceed with RCT

As randomised controlled trials involve a significant organisational and financial input, the decision to progress from a pilot study requires clear and objective measures to ensure that staffing and patients benefit from participation in a study. The use of the guidelines and key information to consider, as proposed by Avery et al. (2017) [41], will influence the evaluation as to whether the trial should progress. The criteria for progression have been identified while considering the usual trial length for a grant funded study (2–3 years), with a projected trial recruitment of 100–150 patients to ensure improvements in clinical significance is achieved [24]. Targets for retention (75%) outcome measure administration (80%) and intervention completion (50%) were identified to minimise impact of missing data while aligning with clinical expectations for this cohort of patients (Table 1).

**Table 1 Tab1:** Progression criteria for RCT

Domain	Proceed with RCT	Proceed with changes to protocol	Do not proceed unless problem resolution
Recruitment	Recruitment of 30 eligible patients within 6 months	Recruitment of eligible patients within 6–12 months	Unable to recruit 30 patients in 12 months
Retention	Minimum of 75% retention to follow-up	Minimum of 50 % retention to follow-up	Less than 50% retention to follow-up
Completion of intervention	At least 50% complete intervention for 40–60 min per day	At least 50% complete intervention for 20–40 min per day	Less than 50% complete intervention for 20 min per day
Outcome measures acceptability	Able to administer 80% of the outcome measures at each time point	Able to administer 80% of the outcome measures at each time point	Able to administer 80% of the outcome measures at each time point
Adverse events	No serious therapy-related adverse events during trial	Less than 5 serious therapy-related adverse events during trial	Five or more serious therapy-related adverse events during trial

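### Cohen's d without a small-sample correction is too large on average by about 3% to 4% at 15 to 11 per arm; Hedges' g removes this bias at no cost

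*Protocol article*

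**What the plan says.** All references are to the protocol article.

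- **Estimator.** Data analysis: "Effect sizes will be calculated using" Cohen's d. No formula is given, and a small-sample correction is neither named nor ruled out.
- **Use.** Data analysis, first objective: "The effect size for the primary outcome variable will be used to determine the required sample size for a fully powered trial". The primary outcome is the FIM.
- **Size.** Sample size: "A sample size of 30 participants has been chosen". Design: "equally randomised controlled trial (1:1". That gives 15 per arm.
- **Attrition.** The proceed column of Table 1 asks for "Minimum of 75% retention to follow-up". Data analysis also plans imputation and says "Previous values from the same patient will be used for missing data".
- **Tests.** Normally distributed continuous variables "will be compared between the groups at each follow-up using an independent groups" t test. Other continuous variables get non-parametric analysis, and categorical variables a chi-square test. Mean differences with 95% CI are reported where appropriate.

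**The concern.** In small samples the pooled SD in the denominator of d makes its expected value exceed the true standardised difference. The direction is always away from zero, and the factor depends only on the degrees of freedom. It is therefore known before any patient is recruited, and a standard multiplier removes it.

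It deserves a remark here because the plan names the statistic and gives it a job: the FIM effect size is to determine how large the next trial is. Required size varies as 1/d², so a proportional error in d is roughly doubled in n. The standardised effects are also what later readers would pool.

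**Working it through.** **Nothing to reproduce.** The total of 30 comes from recommendations for pilot trials. No effect size, SD or power lies behind it.

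**Inputs.** From the article: 30 patients allocated 1:1, so 15 per arm and df = 28. At 75% retention, 15 × 0.75 = 11.25, taken as 11 per arm and df = 20. The significance level is 0.05 ("value of 0.05 will be considered statistically significant"); its sidedness is not stated, and two-sided is assumed. Assumed, because the article gives no figure: true d = 0.5 as the worked case (0.2 to 0.8 as a range), and 80% power for the later trial.

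**Step 1: bias of d.** The exact factor is J(df) = Γ(df/2) / [√(df/2) · Γ((df−1)/2)]. The expected value of d is the true value divided by J, and g = J × d.

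| Per arm | df | J | Mean excess of d (1/J − 1) | Size ratio J² |
|---|---|---|---|---|
| 15 | 28 | 0.9729 | 2.8% | 0.947 |
| 11 | 20 | 0.9619 | 4.0% | 0.925 |

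At true d = 0.5 the expected d is 0.514 or 0.520, a shift of 0.014 or 0.020.

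**Step 2: effect on the later trial's size.** With n per arm = 2(1.960 + 0.842)²/d²:

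- true d = 0.5: 62.8, so 63 per arm;
- expected d at 15 per arm: 62.8 × 0.947 = 59.4, so 60, a shortfall of 5.3% before rounding;
- expected d at 11 per arm: 62.8 × 0.925 = 58.1, so 59, a shortfall of 7.5% before rounding.

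Under the normal approximation, 60 or 59 per arm gives 78.2% or 77.5% power against the 80% intended.

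**Step 3: the bias set against the noise.** Sampling behaviour at true d = 0.5:

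| Per arm | SD of d | Central 95% range of d | Chance d exceeds the truth | RMSE of d | RMSE of g |
|---|---|---|---|---|---|
| 15 | 0.39 | −0.22 to 1.30 | 50.5% | 0.386 | 0.375 |
| 11 | 0.46 | −0.35 to 1.46 | 50.6% | 0.458 | 0.440 |

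The bias is about 4% of the sampling SD (0.014/0.386 and 0.020/0.458). For true d from 0.2 to 0.8, the chance that d exceeds the truth stays between about 50% and 51%.

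**The case against.** Five points can be made against this.

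1. **A stronger reading fails.** A reader might infer that every reported effect is overstated and that any phase III size built on it is too small. The documents and the arithmetic do not support that. The bias is in expectation, about 49% of individual estimates fall below the true value, and many planned sizes would come out too large. Nor does it reach every result: raw mean differences are untouched, and variables analysed non-parametrically or by chi-square are not compared by t test at all. This objection stands in full.

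2. **The article does not say uncorrected.** It gives no formula, and it states that the full protocol is held in the trial registry. That stands as a caution. But the corrected statistic has its own name, so the remark concerns the estimator chosen and not a missing detail. If a correction is already intended, naming it settles the matter.

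3. **An unbiased effect size does not give an unbiased n.** The step from d to n is strongly nonlinear, and the range of d crosses zero. The 5% and 7.5% therefore describe a size computed from the expected d, not the expected planned size. On medians, d is nearer the truth than g at true d = 0.5: 0.505 against 0.491 at 15 per arm, and 0.506 against 0.487 at 11. This is arithmetically right, but it does not outweigh the lower mean bias and lower RMSE of g.

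4. **Eleven per arm may be too pessimistic.** Imputation and values carried forward could keep the analysed number nearer 15, where the bias is 2.8%. They cannot always do so: Table 4 schedules the first FIM at ICU discharge, so a patient who never reaches it has no earlier FIM to carry.

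5. **The larger weakness lies elsewhere.** Sizing a full trial from a point estimate in 30 patients is far more uncertain than any 3% to 4% bias. That stands, and g does not mend it.

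**Conclusion.** The point holds as a minor one. Uncorrected d is too large on average by 2.8% at 15 per arm and 4.0% at 11. A phase III size computed from the expected d would be 5.3% or 7.5% too small, costing about 2 points of power at an assumed true d of 0.5 and 80% power. This rests on normally distributed outcomes with equal variances, on d being computed without a correction, and, for the larger figures, on analysing only completers at exactly the 75% retention target. Sampling error dwarfs the bias. It is worth correcting because its direction and size are known in advance and removing it has no drawback, not because it threatens the trial's conclusions.

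**What to change.** In Data analysis, for outcomes compared by t test, replace Cohen's d with the bias-corrected standardised mean difference (Hedges' g) and its 95% CI. Keep the raw mean difference with its 95% CI alongside. Where the first objective uses the FIM effect size to plan the full trial, use g together with its CI, so that the width of the interval is in view when the size is chosen.

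The cost is a change of wording and one multiplication per estimate: J = 0.973 at 15 per arm, 0.962 at 11. Reported standardised effects become 2.7% to 3.8% smaller (1 − J). No data collection, test or sample size changes.

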Patients will undergo sedation breaks during which targeted early enhanced occupation-based therapy will be delivered. The therapist will carry out the intervention to a maximum of 60 min per day, based on graded performance and localised adaptation from response level, such that sessions may be carried out twice a day (30 min each) to 3 times a day (20 min each) or a single session with a higher level patient (60 min). The measure of 60 min has been chosen to comply with perceived expectations of rehabilitation unit therapy intensity and duration per profession [45]. Where the full quota of therapy is unable to be provided, clear reasons for therapy termination will be gathered on the data form and analysed.

Prior to engaging the patient in early enhanced occupation-based therapy, participants will undergo simple cognitive and physical assessments to enable the therapist to adapt the chosen task to optimise performance and ensure that cognitive stimulation is appropriate. Pre-intervention measures include the following:

Richmond Agitation and Sedation Scale (RASS) [46] measures level of sedation and agitation. Patients will receive treatment if they fall within − 2 to + 2 scales. Patients falling on either extremes are deemed unsuitable for engagement at the current time point, although will be assessed regularly throughout the day prior to therapy, to ensure all opportunities for engagement are taken.

Glasgow Coma Scale (GCS) [47] measures arousal and response level in patients with severe injuries and is used to identify initial emergence of recovery post-sedation withdrawal. The highest score is 15 (fully oriented and alert) and the lowest score is 3 whereby a patient is considered unresponsive. The GCS will be completed prior to the treatment intervention as this will guide the therapist in providing either sensory stimulation [48, 49] or early enhanced occupation-based therapy.

The Confusion Assessment Measure ICU (CAM-ICU) [50] is an assessment of confusion in the early identification of delirium of patients within the intensive care unit. The presence of delirium will not limit participation within an early enhanced occupation-based therapy session. Strategies will be used to increase attention and encourage sequencing of short subtasks in order to complete a full grooming or self-care task.

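### CAM-ICU delirium status is read repeatedly and on different schedules in the two arms, but the plan names only chi-square for categorical data and does not make the patient the unit of analysis

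*Protocol article*

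**What the plan says.** The Secondary outcome measures section of the protocol article lists delirium status by CAM-ICU. Table 4 schedules CAM-ICU daily during the ICU stay and at no later time point. Table 3 treats the result as positive or negative.

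Reading times differ by arm. For controls: "RASS and CAM-ICU scores for the control group participants will be collected daily at 9am". For the intervention arm: "RASS and CAM-ICU scores immediately prior to and following early occupation-based interventions will be collected for additional analysis". The Intervention group section allows one session a day or several: "sessions may be carried out twice a day (30 min each) to 3 times a day (20 min each)". Sessions take place only when RASS lies between −2 and +2, and the Recruitment section staffs therapy Monday to Friday.

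For analysis, the Data analysis section states "Categorical variables will be compared with the chi-square statistic" and "A *p* value of 0.05 will be considered statistically significant". The continuous-data sentence is tied to a time point: "Continuous variables that are normally distributed will be compared between the groups at each follow-up using an independent groups *t* test". The categorical sentence is not. No section of the article defines a per-patient delirium summary such as ever positive, days positive or proportion of days positive.

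**The concern.** Chi-square takes its reference distribution from independent observations. Repeated delirium readings on one patient are not independent, so testing all readings together would overstate the information in 30 patients and give most weight to those who stay longest.

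The second problem does not depend on pooling. The readings whose times the article fixes are not comparable between arms. The intervention arm can have several readings on a treatment day against one for a control. Its readings exist only on days when a session was given, and half of them are taken just after treatment, for which controls have no counterpart. A summary such as ever positive gives the arm with more readings more chances to score positive.

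At stake is a secondary between-arm delirium result, judged at 0.05, that could appear significant with no effect, or be shifted by the reading schedule alone.

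**Working it through.** **Inputs from the article.** Significance level 0.05 (Data analysis); 30 patients (Sample size) at 1:1 (Design), so 15 per arm; reading schedules as above.

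**Assumed, because the article gives none of them.** Readings per patient m, 3 to 10; within-patient correlation (ICC), 0.05 to 0.5; proportion of readings positive, 0.40 in the main simulation.

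**Step 1: the plan's own figure.** With one value per patient (m = 1) the design effect is 1 and the error is 5.0%. A simulation of an uncorrected Pearson chi-square with 15 per arm gave 4.8%. The stated 0.05 is reproduced when the patient is the unit.

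**Step 2: readings tested as collected.** Design effect DE = 1 + (m − 1) × ICC. Actual error = 2 × [1 − Φ(1.96/√DE)]. Example with m = 5 and ICC = 0.3: DE = 1 + 4 × 0.3 = 2.2; 1.96/√2.2 = 1.32; error = 18.6%.

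| m | ICC 0.05 | 0.1 | 0.2 | 0.3 | 0.5 |
|---|---|---|---|---|---|
| 3 | 6.2% | 7.4% | 9.8% | 12.1% | 16.6% |
| 5 | 7.4% | 9.8% | 14.4% | 18.6% | 25.8% |
| 7 | 8.6% | 12.1% | 18.6% | 24.1% | 32.7% |
| 10 | 10.4% | 15.5% | 24.1% | 30.8% | 40.3% |

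Beta-binomial simulation (no effect, 20,000 runs per cell) agrees. At ICC 0.3 it gave 20.1% for m = 5 and 31.8% for m = 10. These rise to 27.4% and 42.5% when the number of readings varies between patients, and to 23.9% and 37.0% when the intervention arm has twice the readings.

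**Step 3: how unequal the schedules are.** A control has 1 reading a day, or 7 in a full week. An intervention patient has 2 readings per session and 1 to 3 sessions, so 2 to 6 readings per treatment day. If every weekday session is given, that is 10 to 30 a week. On days without a session there are none.

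**Step 4: an ever-positive comparison, one value per patient.** Take prevalence 0.40 and ICC 0.2, so a beta distribution with a = 0.4 × 0.8/0.2 = 1.6 and b = 0.6 × 0.8/0.2 = 2.4.

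- Chance of no positive in 3 readings: (2.4 × 3.4 × 4.4)/(4 × 5 × 6) = 0.299.
- Chance of none in 6: 0.299 × (5.4 × 6.4 × 7.4)/(7 × 8 × 9) = 0.152.

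With no treatment effect, about 70% of controls and 85% of intervention patients would be ever positive. Simulated error with m control readings and 2m intervention readings:

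| m | ICC 0.05 | 0.1 | 0.2 | 0.3 | 0.5 |
|---|---|---|---|---|---|
| 3 | 22.1% | 19.4% | 16.9% | 13.4% | 8.5% |
| 5 | 4.9% | 7.2% | 10.4% | 10.2% | 8.0% |
| 7 | 0.4% | 1.6% | 5.4% | 7.4% | 7.7% |
| 10 | 0.0% | 0.2% | 2.0% | 5.0% | 7.3% |

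The low values arise because nearly every patient is positive in both arms. At prevalence 0.3, ICC 0.1 and five control readings, the error was 17%. With the same number of readings in each arm it was at most 5.6%, or 5.8% with varying numbers of readings.

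**Step 5: one proportion per patient.** A t test on per-patient proportions rejected 4.7% to 5.5% of the time. The simulation assumes every reading in both arms has the same chance of being positive. It therefore does not cover bias from reading only on session days or just after therapy; only common reading times deal with that.

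**The case against.** The strongest reply is that the article never says readings will be pooled. The chi-square sentence has ordinary targets that occur once per patient: gender, admission diagnosis, and "hospital discharge destination and support level required on discharge from hospital will be collected from the medical records". Reducing a daily measure to one value per patient is often left to an analysis plan or full protocol, neither of which is shown. All of this stands, and it makes the error rates in Step 2 conditional.

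It is also fair that the session readings are set aside for additional analysis, that nurses record CAM-ICU throughout the day in all patients, and that Table 4 says daily without separating arms. A valid per-patient comparison is therefore possible within the text. But the only reading times the article fixes are 9am for controls and session times for the intervention arm, so the text as it stands points to unlike readings.

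A reader might infer more than the article supports:

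- That false positives will be several times 5%. This needs pooling, which is not stated, and roughly five or more readings at a correlation of 0.2 or more.
- That RASS, GCS and MSQ suffer the same fault under the t test. That test is limited to the follow-up time points, where these measures are not taken.
- That a confidence interval would be too narrow. Intervals are mentioned only with mean differences.
- That the delirium result would decide phase III. Table 1 does not use it, and the sample size is to come from the primary outcome.

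**Conclusion.** The point holds in a limited form. CAM-ICU is a repeatedly measured binary secondary outcome, the arms are read on different schedules, and the only test named for categorical data comes without a unit of analysis. The unequal schedules are in the text and need no assumption.

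The size is conditional. If readings were tested as collected, error would be about 6% to 10% with three readings and a correlation of 0.05 to 0.2, or five readings and 0.05 to 0.1. It would be about 14% to 40% with five to ten readings and a correlation of 0.2 to 0.5. An ever-positive comparison is close to 5% with equal readings, but can be biased against the intervention arm by extra readings. Its error ranged from near zero to about 22% in the settings tried.

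Practical weight is moderate: this is a secondary outcome in a feasibility trial that its Discussion describes as not powered for clinically significant change. The remedy is cheap enough to be worth making.

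**What to change.** Add a short paragraph to the Data analysis section that does four things:

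1. Takes the same routine once-daily CAM-ICU reading in both arms, for example the 9am nursing score, on every ICU day including weekends and days without a session.
2. Reduces it to one value per patient, the proportion of assessed ICU days that are positive, and compares arms with a rank test or a mean difference with 95% CI.
3. Restricts chi-square, or Fisher's exact test where counts are small, to variables recorded once per patient, such as discharge destination.
4. Uses pre- and post-session readings only to describe within-patient change in the intervention arm.

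The cost is the wording, plus extraction of a score that nurses already record; no new assessment is needed. The delirium comparison will be less likely to reach p < 0.05, which reflects the information that 30 patients carry.
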